## Abstract

**ABSTRACT:**

**Introduction:**

Despite the global prevalence of low fertility rates, male contributions to fertility and reproductive health outcomes have been understudied. This study aims to investigate the male contribution to fertility and explore the underlying biological mechanisms. Specifically, we aim to (1) identify male factors associated with successful pregnancy, (2) develop a fertility index incorporating modifiable factors for both males and females to predict pregnancy rate and (3) explore the relationship of male modifiable factors with semen parameters and molecular characteristics.

**Methods and analysis:**

We will conduct an unmatched case-control study involving 240 couples with impaired male fertility (cases) and 240 couples with normal male fertility (controls). Between July 2024 and June 2026, we will recruit 480 eligible couples from KK Women’s and Children’s Hospital, Singapore. Male and female participants will complete questionnaires on sociodemographics, general health and lifestyle factors, and their anthropometry and body fat composition will be measured. Blood and semen samples from the male participants will be collected for biochemical, molecular and semen analyses. Predictive male factors will be identified using the least absolute shrinkage and selection operator method, accounting for female factors. We will construct a logistic regression model incorporating both male and female factors to derive a fertility index, which will be evaluated using cross-validation on subsets of the study population. Multivariable linear regression will be used to explore relationships between male modifiable exposures and semen parameters.

**Ethics and dissemination:**

The study protocol has received approval from the Centralised Institutional Review Board of SingHealth (2024/2120), Singapore. Participants will provide written informed consent. Study results will be disseminated through conferences and peer-reviewed scientific journals.

**Trial registration number:**

NCT06293235.

STRENGTHS AND LIMITATIONS OF THIS STUDYThis unmatched case-control study will comprehensively investigate various factors in males, including biological, clinical, molecular, behavioural and environmental characteristics, to understand their relationships with male reproductive health and outcomes, and provide an important data repository for additional data analyses by the local and international scientific community.The study will use automated technology integrated with artificial intelligence algorithms to measure sperm DNA fragmentation and assess biofluid oxidative status.The participation of Singapore residents from a diverse, multiracial Asian demographic will provide valuable insights with potential relevance to wider Asian contexts.There is a potential for recall bias in self-reported behavioural and lifestyle information, which could affect the predictive accuracy for male fertility status and pregnancy rate.

## Introduction

 Singapore has been grappling with a persistently low total fertility rate of 1.1 since 2018, which dropped below 1.0 in 2023.^1^ Despite the implementation of comprehensive pronatalist policies, this rate remains among the lowest globally, much like many developed countries in the region.^2 3^ Based on the WHO global report, approximately 1-in-6 couples experience challenges in achieving pregnancy.^4^ Subfertility is defined as the failure to achieve conception after 12 months of regular, unprotected sexual intercourse.^5 6^ Given the high prevalence of poor fertility globally, it is crucial to thoroughly examine the factors that impact reproductive health. Historically, fertility research has been primarily focused on women,^7^ but preliminary estimates suggest that males are solely responsible for 20–30% of cases and contribute to 50% overall.^8^ However, our understanding of the causes, impact and consequences of male reproductive health remains inadequate. Emerging reports indicate that men with impaired fertility bear a higher disease burden, with an increased risk of incident diseases such as heart disease and cancer, as well as premature mortality compared with men with normal fertility.^9^ Following the Paternal Origins of Health and Disease (POHaD) concept, as an extension of the Developmental Origin of Health and Disease paradigm, there is increasing evidence suggesting that the father’s health may significantly affect sperm quality and the health of the offspring.^10^,^12^ Consequently, gaining an understanding of the role of male factors in reproductive health is vital for developing effective interventions to address the fertility crisis, informing strategies for male health promotion and management, and potentially leading to improved health of future offspring.

Advanced paternal age has been associated with subfertility, delayed embryo development, increased miscarriage risk and preterm birth, which can be attributable to poor DNA integrity and aberrant DNA methylation in sperm at older age.^13 14^ However, the specific age at which reproductive potential begins to decline remains undefined.^13 15^ Some studies report changes starting around age 40;^16^ others indicate pronounced declines in semen quality by age 50.^13 15^ While certain fertility-influencing factors, such as paternal age, may lie beyond an individual’s control, there are numerous modifiable lifestyle choices and environmental factors that significantly impact male reproductive health and function.^7 17 18^ Studies have shown that high paternal body mass index (BMI), heavy smoking and alcohol dependence increase the likelihood of impaired fertility in males or prolong the time to pregnancy (TTP) for couples.^7 12 19^ These factors have been found to impair sperm count, motility, morphology, DNA integrity and induce oxidative stress.^9 17 19 20^ Furthermore, a study revealed that increased BMI alone did not have a negative influence on semen quality; sperm count and density were only reduced in metabolically unhealthy overweight or obese men, highlighting the role of underlying metabolic function in male fertility.^21^

In terms of diet, high paternal consumption of sugar-sweetened beverages and caffeine has been associated with reduced fecundability.^22 23^ Refined sugars, such as in sweets, and high carbohydrate diets have been linked with reduced sperm concentration and impaired motility;^24^ while caffeine is suggested to negatively impact fertility through DNA defects associated with aneuploidy and DNA breaks.^25^ Low moderate-to-vigorous physical activity and more television watching have been associated with lower total sperm count and concentration.^26^ There is evidence demonstrating an association between higher stress level and poorer semen quality.^27^ Reduced sleep duration has been implicated as a cause of reduced testosterone levels and fecundability.^28 29^ Prolonged sitting and exposure to radiant heat were found to induce testicular heat and oxidative stress, leading to spermatogenesis arrest and sperm DNA damage.^30^ Last but not least, there is increasing interest in endocrine-disrupting chemicals such as bisphenol A and phthalates, which have also been associated with reduced sperm concentration, volume, motility and viability.^31^

Nonetheless, the evidence regarding the relationships of the above-mentioned exposures with human semen parameters, male reproductive function and fecundability obtained from the limited epidemiological studies remains inconclusive and controversial.^7 20^ Many of these studies face challenges in methodology, such as data inaccuracies and reporting bias from maternal reports of paternal factors, relying on BMI for adiposity assessment, fragmented research on individual factors, and were conducted solely in Western or European populations.^7^ Few studies have reported that Asian Americans have decreased success with fertility treatments, including lower pregnancy and live birth rates, which may be attributed to a combination of genetic, environmental and cultural factors.^32^ Moreover, there is a lack of functional or molecular mechanisms explaining the link between these male exposures and fertility. Although semen analysis serves as the fundamental laboratory evaluation of male fertility, the semen parameters based on basic sperm physical characteristics, including motility, density, count, volume and morphology, have been shown to be poor predictors of reproductive outcomes and are not able to reliably discriminate between men with fertility issues.^33^ Increasing evidence suggests that markers of sperm DNA integrity may help differentiate men with impaired fertility from those with normal fertility.^34^ The WHO recommends including sperm DNA fragmentation as an extended parameter to better evaluate male fertility.^35^ Single- and double-stranded DNA breaks in sperm have different reproductive consequences.^36^ Increased reactive oxygen species causes single-stranded DNA breaks in sperm. Sperm DNA fragmentation induced by elevated oxidative stress has been proposed as the link between male obesity and impaired fertility.^14^ Double-stranded DNA breaks in sperm have been linked with suboptimal embryo development, poor implantation rates and recurrent miscarriage in couples without a female factor.^37^,^39^ Together with sperm gene expression and DNA methylation, there may be epigenetic signatures in predicting reproductive outcomes and future offspring health.^20 40 41^

Therefore, in this study, we will comprehensively examine male factors of fertility, in particular, modifiable exposures, including behavioural, lifestyle and environmental factors, as well as metabolic and stress indicators. For semen parameters, in addition to basic sperm physical characteristics, we will measure sperm DNA fragmentation, DNA methylation and gene expression, as well as seminal plasma oxidative status. Information generated from these data will provide valuable insights regarding their specific relationships with male fertility and reproductive success. Importantly, the study of sperm molecular features has potential implications not only for reproductive outcomes but also for intergenerational effects, predisposing to offspring phenotypes.^20 42^ The conceptual framework of this study is presented in figure 1.

**Figure 1 F1:**
[figure not shown]
Conceptual framework of the study. The successful outcomes of reproductive health depend not only on female factors but also on male factors, which include behavioural, lifestyle, metabolic and stress exposures, as well as semen parameters. Specifically, sperm molecular characteristics such as oxidative stress, epigenetic signatures including DNA methylation and gene expression may play a role in explaining the connection between male exposures, fertility and the health of offspring.

### Objectives

The overall objective of this study is to determine the contribution of male factors to successful pregnancy after accounting for female factors and gain a deeper understanding of the biological mechanisms that underlie this relationship. Specifically, we aim to:

Identify male factors associated with the likelihood of pregnancy, independent of female factors.Develop a fertility index that integrates modifiable factors for both males and females to estimate the likelihood of pregnancy.Explore the relationships between male modifiable factors, oxidative status, sperm physical and molecular characteristics.

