### Data collection and management

During the study visit (the only single timepoint visit), trained research staff will collect data on the sociodemographics and medical history of participants through interviews and medical record collection forms. They will also gather self-reported data on behavioural, lifestyle and environmental factor exposures from the past month using standardised questionnaires. The selection of the recall timeframe is based on the period specified in the validated questionnaires (table 1). Additionally, the staff will conduct anthropometric and body fat composition measurements, and collect blood, urine and semen samples from participants at the clinics in KKH. All data will be saved in a REDCap database. Access to this database is secured with a password, and only approved study team members can access the stored information.

**Table 1 T1:** Data and biosamples collected from both case and control participants

Male partners	Parameters
Sociodemographic, clinical, behavioural, lifestyle and environmental factors	Age, country of origin, length of time in Singapore if born overseas, ethnicity, education, occupation, monthly income, medical history, medication, family history, reproductive health history, male sexual function,^60^ environmental exposure, cigarette smoking, sleep,^61^ stress,^62^ dietary supplement intake, dietary and alcohol intake,^63^ chrononutrition profile,^64^ physical activity,^65^ sedentary behaviour
Anthropometric and blood pressure measures	Body height, weight, body fat composition (InBody 970, USA), blood pressure
Biochemical tests (blood/urine samples)	HbA1c, lipid profile, cortisol, oxidative stress, inflammatory biomarkers, environmental pollutants (endocrine-disrupting chemicals), exosomes, microbial-derived metabolites
Semen analysis	Semen volume, sperm density, sperm motility, sperm morphology, sperm DNA fragmentation
Molecular analysis	mRNA expressions, sncRNA expression, DNA methylation

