**Female partners**	
Sociodemographic, clinical, behavioural, lifestyle and environmental factors	Age, country of origin, length of time in Singapore if born overseas, ethnicity, education, occupation, monthly income, medical history, medication, family history, reproductive health history, female sexual function,^66^ environmental exposure, cigarette smoking, sleep,^61^ probable depression,^67^ dietary supplement intake, dietary and alcohol intake,^63^ chrononutrition profile,^64^ physical activity,^65^ sedentary behaviour
Anthropometric and blood pressure measures	Body height, weight and body fat composition (InBody 970, USA), blood pressure

HbA1c, glycated haemoglobin; sncRNA, small non-coding RNA

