### Biosampling and biomarker analyses

Male partners of participating couples will be requested to provide peripheral blood, urine and semen samples during their study visit. The blood samples will be processed and analysed for metabolic and stress biomarkers at the biochemical laboratory of KKH within 1–2 hours. The semen samples will be obtained through masturbation after a period of 2–3 days of sexual abstinence. They will be collected in sterile 50 mL non-spermiotoxic polypropylene containers and allowed to liquefy at room temperature. Once the semen has liquefied, basic semen parameters, including volume, density, motility and morphology, will be evaluated in the semen analysis lab of KKH using the LensHooke X12 Pro Semen Analysis System (X12, Bonraybio, Taiwan), following the criteria established by the WHO.^44^ Single- and double-stranded DNA breaks in sperm will be measured using the sperm chromatin dispersion assay (LensHooke R10 Plus kit) and sperm DNA fragmentation releasing assay (LensHooke R11 Plus kit), respectively.^45^ Oxidative status of blood and seminal plasma will be assessed using the point-of-care NMR system.^46 47^ Additional blood and semen samples will be stored at −80°C for future analyses such as inflammatory biomarkers, environmental chemicals and other related biochemical markers.

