We will include the identified male factors from aim 1, along with female factors which are known to be associated with successful pregnancy in a multivariable logistic regression. The male factors will focus on those easily accessible measurements. The female factors include age, BMI, smoking exposure, dietary habit, alcohol consumption and folic acid supplementation, which we have identified in our previous study.^52^ We will also include some important clinical data and other maternal factors such as the duration of active conception attempts, sexual health issues and probable depression in the logistic regression to further select the predictors. To ensure accuracy, we will use weighted logistic regression, adjusting the model based on the updated prevalence of successful pregnancies within a year in the population to correct for sampling biases. The best-fitting model will be determined using Akaike’s information criteria. Subsequently, we will create a point-based scoring system based on the final model coefficients,^53^ making it easily applicable in community settings. Integer points will be assigned depending on the presence or absence of each factor, allowing the estimation of overall probability by summing the points. Higher point values will indicate higher chances of pregnancy. To facilitate calculation of the fertility index score, all continuous variables will be categorised based on clinical thresholds or appropriate percentiles prior to the analysis. We will repeat the same procedures by including male metabolic biomarkers and semen parameters that are associated with successful pregnancy in the weighted logistic regression. This will enable the generation of various versions of the fertility index, catering to different levels of complexity for application in primary and tertiary care settings.

Subsequently, we will use 10-fold cross-validation to assess the performance of the derived logistic regression models and respective fertility index scores. This cross-validation procedure helps evaluate the model’s performance on different subsets of the data, providing an estimate of its predictive ability and generalisation performance. The fertility index will be evaluated for its discriminatory ability in predicting chances of pregnancy based on the area under the receiver operating characteristic curve (AUROC), with value >0.80 indicating that the model exhibits a good discriminatory ability or predictive value.

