Given that the fertility index comprises male and female factors, we will perform additional analyses to evaluate the individual performance of the index that includes only male factors or female factors using the AUROC. We will also evaluate the performance of the male factor index, with adjustment of female factor index.

#### Aim 3

We will use multivariable linear regression to examine the association between modifiable factors and semen parameters, adjusting for sociodemographic factors.

To understand the relationships between male factors and fertility indices across different conception methods, we will replicate the above analyses by examining outcomes based on assisted and unassisted conception. To assess potential selection bias in both studies, we will compare baseline characteristics between participants with and without a complete set of data. We will use multiple imputation by chained equation to handle missing values.^54^ Sensitivity analyses will be conducted using only samples with complete data. To further ensure robustness, we will test interactions between male and female factors and stratify analyses by key confounders. Statistical analyses will be conducted using the Stata Statistical Software.

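### The additional Aim 2 analyses can overstate the male contribution: extended indices lack female biosample data, and the male index is adjusted for a coarse female points index

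*Protocol article*

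**What the plan says.** All references are to the protocol article.

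- **Objectives.** The overall objective is to "determine the contribution of male factors to successful pregnancy after accounting for female factors".
- **Who is sampled.** The Abstract says "Blood and semen samples from the male participants will be collected for biochemical, molecular and semen analyses". Biosampling and biomarker analyses says "Male partners of participating couples will be requested to provide peripheral blood, urine and semen samples during their study visit". Data collection and management speaks of samples from participants in general, but Table 1 settles it. Men have a biochemical row ("HbA1c, lipid profile, cortisol, oxidative stress, inflammatory biomarkers, environmental pollutants (endocrine-disrupting chemicals), exosomes, microbial-derived metabolites") plus semen and molecular rows. The female block holds questionnaire and clinical items and then "Body height, weight and body fat composition (InBody 970, USA), blood pressure", with no biochemical row.
- **Statistical analysis plan, Aim 2, index versions.** The basic index relies on male measurements that are easy to obtain. Then: "We will repeat the same procedures by including male metabolic biomarkers and semen parameters that are associated with successful pregnancy". No female counterpart is added.
- **Aim 2, scoring.** Every continuous variable is categorised before the analysis, and "Integer points will be assigned depending on the presence or absence of each factor".
- **Aim 2, additional analyses.** A male-only and a female-only index are each judged by AUROC, and "We will also evaluate the performance of the male factor index, with adjustment of female factor index". Neither step is confined to the basic version.
- **Elsewhere.** Aim 1 adjusts for female factors as covariates chosen with directed acyclic graphs. The joint Aim 2 model enters female factors as predictors before points are assigned.
- **Discussion.** The limitations cover recall bias, residual confounding in general and generalisability. They do not mention the imbalance in biosamples.

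**The concern.** The additional Aim 2 analyses are the one place where the predictive performance of the two partners is set side by side, so readers will look there for the size of the male contribution. Two features can enlarge it.

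1. **Unequal measurement.** In the extended versions the man is described by lifestyle, blood and semen, and the woman by lifestyle and anthropometry. A higher male-only AUROC may then show only that more was measured in him. If partners' biology is correlated, a male marker also picks up part of the unmeasured female effect.
2. **Coarse adjustment.** A female score built from categories loses, for example, the age differences within a class. Partners' ages are correlated, so a male age item can carry what the female score misses.

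At stake is a statement that male factors add to, or outweigh, female factors when part of that result comes from the measurement and the coding.

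**Working it through.** **Inputs.** From the article: 240 cases and 240 controls, men aged 21-49, women aged 21-39, and the scoring rules above. The article gives no effect sizes, partner correlations or category cuts for this question, so those below are assumptions.

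**The plan's own figure.** The 240 per group reproduces: 2 x (1.960 + 1.282)^2 x 4^2 / 1.3^2 = 199 per group, 398 in total (stated 400); 398 x 1.2 = 478 (stated 480). It is not in dispute and serves only as the study size in step 3.

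**Step 1. Male-only against female-only AUROC.** Model: logit(p) = bL (L_m + L_f) + bB (B_m + B_f), where L is lifestyle, B is biology, m and f are the partners, and B is observed in men only. Assumed: bL 0.4-0.5 and bB 0.5-0.7 log odds per SD, identical in both partners.

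| Partner correlation | Male-only (L and B) | Female-only (L) |
|---|---|---|
| 0 | 0.65-0.69 | 0.59-0.61 |
| 0.2 | 0.68-0.72 | 0.60-0.63 |

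On lifestyle alone, at correlation 0.2, the two partners agree within about 0.002. The gap therefore comes from what was measured, and it does not need partner correlation.

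**Step 2. Male gain over the female block.** All four effects are set to 0.5 log odds per SD, with 200,000 couples. The entry is the log-likelihood gain from adding the male block to the female block, divided by the gain of the whole model; the AUROC gain is in brackets.

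| Female block | Correlation 0 | 0.2 | 0.4 |
|---|---|---|---|
| Lifestyle and biology | 0.52 (0.072) | 0.43 (0.061) | 0.32 (0.046) |
| Lifestyle only, continuous | 0.67 (0.088) | 0.65 (0.091) | 0.61 (0.090) |
| Lifestyle only, tertile points | 0.72 (0.097) | 0.70 (0.104) | 0.67 (0.106) |

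Two boundary checks:

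- **No true male effect.** With female biology omitted, the male marker's log odds ratio is 0.082 at correlation 0.2 (exp(0.082) = 1.09 per SD), 0.186 at 0.4 (exp(0.186) = 1.20), and essentially zero at 0.
- **Female biology carries no signal.** At correlation 0.2, omitting it moves the share only from 0.58 to 0.60.

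**Step 3. Adjustment for a coarse female score.** Samples of 240:240; male age has no effect; female age has an odds ratio of 1.05-1.12 per year; partner age correlation is 0.6-0.8; ages are truncated to the eligible ranges. The entries are the percentage of studies in which the male age item is significant at 5%. In the right-hand column the assumed mean and SD are 32 and 4 years for women and 34.5 and 5 for men.

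| Female age in the adjustment | Both ages cut once, at 35 | Male points cut at 35 and 40 |
|---|---|---|
| One cut, at 35 | 7-34% | 7-30% |
| Two cuts (30 and 35 in the right-hand column) | 3-9% | 5-8% |
| Quartiles | not run | 4-6% |
| In years | 3-5% | 4-6% |

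The excess appears with the same cut in both partners, so it does not come from giving men the finer coding. It nearly disappears once female age has two or more cuts.

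**The case against.** **Female factors are handled properly elsewhere.** This stands. A reader might infer that female factors enter the study only as a points score. The article does not support that: Aim 1, which answers the aim of male factors independent of female factors, uses them as covariates, and the joint Aim 2 model uses them as predictors, though categorised. The score is the adjustment variable only in the additional Aim 2 analyses.

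**The basic index is already close to like for like.** This also stands. It uses easily accessible male measurements, and Table 1 records nearly the same questionnaire, anthropometry and blood pressure items in both partners. The extended versions are offered for different care settings, not as the measure of the male contribution. But the male-only versus female-only comparison is not restricted to the basic version.

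**Both directions can be derived.** Combined minus male-only AUROC gives the female gain. That is true, so the request is only to report it explicitly. Adjusting male for female also matches the objective.

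**The simulations build in their result.** Partly right. Step 1 assumes that female biology matters. Semen analysis has no female equivalent, so the comparable gap is blood and urine markers. Female infertility exclusions among cases narrow female biology, and control women are pregnant at the visit, so their blood markers could mislead. These are reasons not to read the figures as forecasts and not to ask for female samples. They do not make the extended AUROC comparison like for like.

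**Category cuts are detail, and men are categorised too.** The article fixes no number of classes, so the upper end of step 3 is not a property of the plan. Coarsening the male variables, however, does not remove the confounding left by a coarsened female covariate.

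**Conclusion.** The point holds for the additional Aim 2 analyses and the extended index versions. There the apparent male contribution can be overstated.

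- **Unequal measurement.** The AUROC gap is 0.68-0.72 against 0.60-0.63 for partners with equal assumed effects. It depends on female biology carrying signal. Bias in a male marker's coefficient also needs partner correlation.
- **Coarse score.** False-positive rates for a null male age item are 7-34% with one female age cut, 3-9% with two and 3-5% with age in years. The problem is material only if the categories are very coarse, which scoring by presence or absence permits but does not require.

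A reader might go further and infer that the study's male share is overstated throughout, or that it is set to conclude that men contribute more than women. The article supports neither. It plans no male share and no such claim, Aim 1 does not adjust through the score, and the distortion is a risk under stated assumptions rather than a demonstrated bias.

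**What to change.** In the additional Aim 2 analyses:

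1. Evaluate the male index adjusted for the individual female factors, with female age and BMI continuous, instead of for the female points index.
2. Make the male-only versus female-only AUROC comparison on the index version built from measures recorded in both partners. Report the gain in both directions, male added to female and female added to male, on the same cross-validation folds.
3. Describe the biomarker and semen versions as the added value of male tests, not as the male contribution.
4. Add to the limitations that biosamples come from men only.

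The cost is some wording and a few more model fits on data already planned; no new data collection is needed. The downside is that the reported male contribution will probably be smaller.

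### Aim 2 presents the fertility index as one of modifiable factors, but no stated analysis shows what the modifiable factors contribute to its AUROC

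*Protocol article*

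**What the plan says.** The Objectives section of the protocol article sets the second aim as: "Develop a fertility index that integrates modifiable factors for both males and females to estimate the likelihood of pregnancy". The abstract puts it almost identically: "develop a fertility index incorporating modifiable factors for both males and females to predict pregnancy rate". The Introduction draws the line between fixed and modifiable factors itself: "While certain fertility-influencing factors, such as paternal age, may lie beyond an individual’s control".

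The Aim 2 part of the Statistical analysis plan section builds the index from three sources:

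- Male factors carried over from Aim 1, restricted by ease of measurement: "The male factors will focus on those easily accessible measurements".
- A list of female factors that begins with age: "The female factors include age, BMI, smoking exposure, dietary habit, alcohol consumption and folic acid supplementation".
- Further candidates, namely important clinical data and "other maternal factors such as the duration of active conception attempts, sexual health issues and probable depression".

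An AUROC above 0.80 is then taken as good discrimination for the resulting index. Further versions add male metabolic biomarkers and semen parameters: "This will enable the generation of various versions of the fertility index, catering to different levels of complexity". The component analysis is by partner. It will "evaluate the individual performance of the index that includes only male factors or female factors using the AUROC", and will also assess the male index adjusted for the female index. The analyses are repeated by assisted and unassisted conception.

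**The concern.** The aim singles out factors that couples can change. The analysis selects predictors by accessibility and known association, and every planned breakdown cuts along another line. The female part certainly mixes fixed and changeable items, since age sits beside BMI, smoking, diet, alcohol and folic acid. No stated result gives the discrimination of the modifiable factors alone, or their gain over the fixed ones.

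The interpretation of Aim 2 is at stake. If the index passes 0.80, a reader of the objective will naturally take this as a finding about modifiable factors. The Discussion encourages that reading, because it ties the study to optimising men's health before conception. The planned output could not tell an index carried by changeable behaviour from one carried by age or history.

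**Working it through.** **The plan's own figures.** The Sample size section assumes a BMI difference of 1.3 kg/m², SD 4, two-sided 5% and 90% power. The normal formula, n per group = 2(z₀.₉₇₅ + z₀.₉₀)²(4/1.3)², gives 199. The t-based version gives 199.9, hence the stated 200. Multiplying by 1.2 gives 240 per group, 480 couples. The figures reproduce, so the BMI effect can serve as the protocol's own measure of one modifiable factor: d = 1.3/4 = 0.325.

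**From effect size to AUROC.** For normal predictors with equal variance in both groups, AUROC = Φ(d/√2). Independent predictors combine as d = √(Σdᵢ²).

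- BMI alone: Φ(0.325/√2) = 0.59.
- Needed for 0.80: d = √2 × z₀.₈₀ = 1.19. With BMI in the model, the rest must supply √(1.19² − 0.325²) = 1.15.
- k independent factors as strong as BMI, Φ(0.325√k/√2):

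| k | AUROC |
|---|---|
| 1 | 0.59 |
| 5 | 0.70 |
| 10 | 0.77 |
| 13 | 0.796 |
| 14 | 0.805 |

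About 14 are therefore needed to pass the benchmark on modifiable factors of that strength alone.

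**What fixed or history items could supply.**

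- *Female age.* The documents give no SD, so I assume 3.5 to 4.5 years. A 2-year difference between groups gives AUROC 0.62 to 0.66, and a 4-year difference gives 0.74 to 0.79. Reaching 0.80 on age alone takes 1.19 × 3.5 = 4.2 to 1.19 × 4.5 = 5.4 years.
- *Duration of attempts.* Cases must have tried for at least 12 months, and controls must have conceived within 12 months (Inclusion criteria). If the variable records that same attempt, the groups can overlap only at exactly 12 months. With a share p of each group there, AUROC = 1 − p²/2: 0.995 for p = 10% and 0.98 for p = 20%. Dichotomised at 12 months with 10% misclassified in each group, it is 0.90. Any of these passes 0.80 alone.

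**An illustration of a mixed pass.** Suppose the fixed factors have AUROC 0.78 and the modifiable factors 0.64. Then d = 1.09 and 0.51, which combine to √(1.09² + 0.51²) = 1.20, so AUROC = 0.803. The index passes, with an increment of 0.803 − 0.78 = 0.023 from the modifiable part. These inputs are illustrative. Other plausible pairs fall short: 0.75 with 0.65 gives 0.781, and 0.78 with 0.62 gives 0.797.

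**The case against.** The strongest reply is that nothing here is contradicted. A reader might infer that the objective restricts the index to modifiable factors, so that the Aim 2 model breaches it. The text does not support that. It speaks of integrating or incorporating such factors, never of using only them, and the stated purpose is to estimate the chance of pregnancy. Five of the six listed female factors are modifiable, and age belongs in a sensible prediction tool. The 0.80 benchmark is attached to the index as a whole, and the document nowhere says that passing it would show modifiable factors to be responsible. All of this stands.

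The split by partner also serves the overall objective, which is the male contribution after accounting for female factors. That justifies the split, but it does not answer the second aim as worded. Aim 1 estimates associations of male factors, and Aim 3 relates modifiable factors to semen parameters. Neither measures how well both partners' modifiable factors predict pregnancy.

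Two further cautions are fair. Whether male age enters the male index is not stated, because Aim 1 treats male sociodemographics as confounders. Sexual health issues and probable depression are not plainly unchangeable. Both support classifying predictors in advance.

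A secondary breakdown can often be left to a separate analysis plan, which is not shown. But the article does state its breakdowns and its benchmark, and those stated do not isolate the factors that the aim names.

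**Conclusion.** The point holds as a mismatch of emphasis between aim and analysis, to be corrected cheaply. It does not invalidate the index. As planned, an AUROC above 0.80 could not be attributed to modifiable factors. The protocol's own BMI effect gives an AUROC of about 0.59 for one factor, with about 14 independent ones of that size needed to pass 0.80.

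Those figures assume normal, equal-variance, independent predictors. Stronger factors would lower the count. Positive correlation among factors of equal strength would raise it.

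A reader might also infer that fixed factors will in fact carry the index past 0.80. The documents do not show this. Age alone would need a difference of roughly 4 to 5 years under an assumed SD, and the 0.78 and 0.64 pair is not taken from the protocol. Duration of attempts is the exception, since the eligibility rules alone put it near 1, but it is a candidate that enters only if selected.

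**What to change.** 1. Before analysis, class every candidate predictor as fixed (such as age) or modifiable, and record where the less obvious items, such as sexual health issues and probable depression, are placed.
2. Leave duration of conception attempts out of both sets. If it sat in the fixed set, that set's AUROC would be close to 1 and the increment from modifiable factors close to zero by construction.
3. On the same cross-validation folds, report the AUROC of (a) the fixed set, (b) the modifiable set and (c) both together, with the increment (c) − (a) and its 95% CI.
4. Base any statement about modifiable factors on (b) and that increment. Keep the combined index, without duration, as the prediction tool, and keep the planned split by partner.

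This needs no new data and no change in sample size. The cost is two extra model fits and a figure for the modifiable part that will probably look less favourable than that for the whole index.
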